### Substudy flow and non-respondent analyses

Participation in the substudy on walking activity and life-space was offered to all the study participants during the face-to-face interview. Figure
3 shows the flowchart of the substudy. In total, 364 diaries were returned, of which nine were excluded. In addition, 190 participants were willing to wear an accelerometer in addition to keeping the diary. Of these, 179 participants returned a valid diary. Unfortunately, the accelerometer battery ran out during the measurements in three cases and one case wore the accelerometer occasionally; hence these four were included in the diary-only group. Thus in total, the accelerometer group consisted of 175 participants and the diary-only group of 359 participants.

**Figure 3 F3:**
[figure not shown]
Flow chart of the substudy.

The participants in our substudy groups were somewhat younger than those not participating in the substudy (accelerometer group 80.4 ± 4.2, diary-only group 79.9 ± 4.1, vs. not in substudy 81.4 ± 4.4, ANOVA p <0.001). In addition, the participants in the substudy groups reported less difficulty in outdoor mobility (Chi-square test p < 0.001) and going outdoors more frequently (p < 0.001). Those participating in the diary-only subgroup lived more frequently in an apartment block (p = 0.008), in addition, they more often lived with another person (p = 0.009). The gender distribution and self-rated health were not significantly different between the three groups. Baseline assessment of level of physical activity showed that 36.6% of those in the accelerometer group and 44.4% of those in the diary only group participated in moderate to strenuous physical activity for at least 4 hours a week or in physical exercise multiple times a week compared to 21.0% of those not participating in the substudy (<0.001).

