### Data management and statistical analysis

#### Statistical analyses

In this study, when inferential analyses are conducted for continuous variables, they will primarily be based on parametric general linear models such as multiple regression and analysis of variance. Markedly non-normally distributed data will be transformed prior to inferential comparisons. For variables that cannot be successfully transformed, nonparametric methods will be used. Categorical variables will be analyzed with logistic regression or categorical response models. If the expected frequencies are too small for asymptotic assumptions, exact testing techniques will be used.

Data will be analyzed using multivariate statistical methods which allow analyses of time-dependent outcomes and covariates. In longitudinal analyses, we will use approaches which take into account mortality as a competing risk for other health outcomes. Person-environment interaction will be analyzed with help of regression analyses. Path modeling and structural equation modeling will be used for multilevel analyses of environmental and individual characteristics relative to the study outcomes. Generalized estimating equations (GEE) models will be used to analyze differences in changes in prevalence over three time points. The level of statistical significance will be set at p < 0.05 (two-sided).

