**Figure 2 F2:**
[figure not shown]
Flow chart of the study.

In total, 811 of those who declined to participate and 833 of those who participated in the study, responded to the initial phone interview were included in the non-respondent analyses (n = 1644). Those who declined to participate were older (81.2 ± 4.1 vs. 80.4 ± 4.2, Students T-test p < .001), more often lived with a spouse or others (Chi-square test p = .006), more often perceived their health as poor or very poor (p < .001), perceived more difficulties in outdoor mobility (p < .001) and moved outdoors less often than those who participated in the study (p < .001) (Table
2).

**Table 2 T2:** Non-respondent analyses and subgroup analyses

	**Total sample**			**Substudy**			
	**Non-participants**	**Participants**	***Chi-square***	**Accelerometer**	**Diary-only**	**Not in substudy**	***Chi-square***
	(n = 811)	(n = 833)	*P-value*	(n = 170)	(n = 354)	(n = 309)	*P-value*
**Gender** (women)	66.1	62.1	.089	63.5	59.3	64.4	0.367
**Housing type**			.511				0.008
Apartment block	56.7	55.9		49.4	60.7	54.0	
Row house	14.5	16.6		19.4	17.8	13.6	
Semi-detached/ detached house	28.7	27.5		31.1	21.4	32.4	
**Living situation**			.006				0.009
Alone	49.7	53.9		55.3	49.7	57.9	
With spouse	44.2	43.1		44.1	47.7	37.2	
With other person	6.1	3.0		0.6	2.5	4.9	
**Self-rated health**			<.001				0.056
Very good	3.0	5.3		7.1	5.9	3.6	
Good	25.2	32.5		35.2	34.5	28.8	
Moderate	49.9	52.3		52.9	50.3	54.4	
Poor	19.9	9.7		4.7	9.3	12.9	
Very poor	2.0	0.1		0	0	0.3	
**Difficulty in outdoor mobility**			<.001				<0.001
No difficulties	52.5	60.5		67.1	62.7	54.4	
Minor difficulties	30.4	28.9		30.6	28.2	28.8	
Major difficulties	10.6	8.0		2.4	7.1	12.3	
Unable with / without help	6.4	2.5		0.0	2.0	4.5	
**Frequency of outdoor mobility**			<.001				<0.001
Daily	63.5	75.9		84.1	77.1	69.9	
4-6 times/week	15.2	13.0		13.5	13.0	11.0	
1-3 times/week	13.5	8.8		1.8	8.5	12.9	
< once /week	7.9	2.4		0.6	0.3	4.5	

Sample characteristics represented as proportions (%) and tested group differences.

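### Table 2 uses an asymptotic chi-square for self-rated health where the plan's own rule calls for an exact test; the exact test reverses the non-significant verdict

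*Protocol article*

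**What the plan says.** Under Statistical analyses, the protocol article fixes the significance level: "The level of statistical significance will be set at p < 0.05 (two-sided)." In the same section it gives a rule for sparse categorical data: "If the expected frequencies are too small for asymptotic assumptions, exact testing techniques will be used."

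Table 2, in Study flow and non-respondent analyses, compares three groups defined by substudy participation: accelerometer (170), diary-only (354) and not in substudy (309). The footnote describes the content as "Sample characteristics represented as proportions (%) and tested group differences", and the p-value columns are headed as chi-square. The self-rated health line reads "Self-rated health <.001 0.056", where the second figure belongs to the three-group comparison.

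Substudy flow and non-respondent analyses then states: "The gender distribution and self-rated health were not significantly different between the three groups." The same paragraph reports significant differences in age, outdoor mobility, housing, living situation and physical activity.

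**The concern.** Self-rated health has five categories, and one person in the whole table chose the lowest. Spreading one person over three groups creates cells with expected counts far below 1, where the chi-square approximation is unreliable. The row also adds two degrees of freedom while carrying almost no information. The printed p-value lies just above 0.05, so the choice of test can decide the verdict.

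What is at stake is the account of substudy selection. The substudy concerns walking activity and life-space mobility, to which health is plainly relevant. The text puts self-rated health beside gender as a variable without a significant difference, and so leaves it off the list of characteristics on which substudy members differ from the rest.

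**Working it through.** **Inputs.** Percentages and group sizes come from Table 2; the test rule and the 0.05 level come from Statistical analyses. Each count is percentage × group size / 100, rounded. One person is 0.28 to 0.59 percentage points, so the counts are unambiguous. For the top category, "Very good 3.0 5.3 7.1 5.9 3.6" gives 7.1% of 170 = 12, 5.9% of 354 = 21 and 3.6% of 309 = 11.

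| Group | Very good | Good | Moderate | Poor | Very poor | Total |
|---|---|---|---|---|---|---|
| Accelerometer | 12 | 60 | 90 | 8 | 0 | 170 |
| Diary-only | 21 | 122 | 178 | 33 | 0 | 354 |
| Not in substudy | 11 | 89 | 168 | 40 | 1 | 309 |
| All | 44 | 271 | 436 | 81 | 1 | 833 |

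The rows sum to the printed group sizes, and the bottom line returns the printed participants column (5.3, 32.5, 52.3, 9.7 and 0.1%). The only mismatch is 35.2 printed for 60/170 = 35.29, a truncation.

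**Step 1: reproduce the printed figure.** Pearson X² = Σ(O − E)²/E with E = row total × column total / 833 gives X² = 15.15 on (3 − 1)(5 − 1) = 8 df, p = 0.0562. This matches 0.056, so the asymptotic five-category test is the one that was run.

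**Step 2: expected counts in the lowest category.** 170 × 1/833 = 0.20; 354 × 1/833 = 0.42; 309 × 1/833 = 0.37. These are the only cells of the 15 below 5, and all three are below 1. Together they contribute 1.70 of the 15.15 and cost 2 df.

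**Step 3: apply the stated rule.** Exact conditional tests with all margins fixed, by Monte Carlo with 400,000 tables (standard error about 0.0003):

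- Fisher-Freeman-Halton: p = 0.031
- exact Pearson: p = 0.043

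**Step 4: remove the sparseness instead.** Merging poor and very poor gives a 3 × 4 table with smallest expected count 170 × 44/833 = 9.0. Pearson X² = 14.04 on 6 df, p = 0.029. Here the asymptotic test is sound, and it agrees with the exact results.

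**Step 5: size and location of the difference.** Poor or very poor: 8/170 = 4.7%, 33/354 = 9.3%, 41/309 = 13.3%. Pairwise chi-square tests on the merged table, unadjusted for multiplicity:

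- accelerometer versus not in substudy: p = 0.007
- diary-only versus not in substudy: p = 0.09
- accelerometer versus diary-only: p = 0.32

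The gender part of the sentence stands: the printed p = 0.367 is reproduced.

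**Separate clerical check.** In the outdoor-frequency block, diary-only sums to 77.1 + 13.0 + 8.5 + 0.3 = 98.9%, and not in substudy to 69.9 + 11.0 + 12.9 + 4.5 = 98.3%. Rebuilt counts total 350 and 304, that is 4 and 5 short. Against the participants column, 4–6 times a week gives 23 + 46 + 34 = 103 where 13.0% of 833 is 108, and less than once a week gives 1 + 1 + 14 = 16 where 2.4% of 833 is 20. Setting diary-only less than once a week to 5/354 = 1.4% and not-in-substudy 4–6 times a week to 39/309 = 12.6% closes every total. The p-value is below 0.001 before (2 × 10⁻⁶) and after (8 × 10⁻⁵).

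**The case against.** The best defence is that nothing is miscalculated. The 0.056 is correct for the test that was run, the text says only that significance was not reached, and Table 2 prints every percentage, so the gradient is open to any reader. The shift from 0.056 to between 0.03 and 0.04 is modest, in a descriptive table. The article already discloses that substudy members were younger, more mobile outdoors and more active. It could also be said that the exact-test rule was written for the study's main analyses and sets no threshold for what counts as too small.

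Much of this stands as a limit on the size of the point. It does not rescue the sentence. Expected counts below 1 are too small by any customary standard, and both usual exact tests and the merged table fall below the level that the article sets.

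Three stronger readings are tempting and are not supported:

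- A reader might infer that the article declares substudy selection unrelated to health. It does not; it reports a non-significant test.
- A reader might infer that substudy analyses will therefore leave out a needed adjustment. The article describes no selection adjustment or weights for the substudy, so there is nothing to amend, and such detail may sit in a document not shown.
- A reader might conclude that both substudy groups were healthier than the rest. The pairwise results support this only for the accelerometer group.

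Tests that use the ordering of the categories give smaller p-values (Kruskal-Wallis 0.004, linear-by-linear 0.0006). The article does not prescribe them for this table, so they do not measure the departure from its rule.

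**Conclusion.** The point holds, at modest size. Under the article's own rule the three-group comparison of self-rated health has p of about 0.03 to 0.04 rather than 0.056, and the non-significant verdict reverses at two-sided 0.05. The supported statement is that self-rated health differed between the groups, with the clearest contrast between accelerometer wearers and those outside the substudy.

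This rests on two assumptions: that the rebuilt counts are right, which the margins and the reproduced p-value bear out, and that expected counts of 0.20 to 0.42 meet the article's undefined condition of being too small. The life-space and quality-of-life outcomes, the sample size and the main-cohort analyses are untouched. The outdoor-frequency cells are a real but separate clerical matter and add no weight to this point.

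**What to change.** 1. In Table 2, replace 0.056 with an exact p-value and name the test in the footnote. Choose one exact statistic and say which; merging the two lowest categories is an acceptable alternative if stated.
2. In Substudy flow and non-respondent analyses, keep the gender statement and say that self-rated health differed between the groups, giving poor or very poor as 4.7% (accelerometer), 9.3% (diary-only) and 13.3% (not in substudy).
3. List self-rated health with age, outdoor mobility and physical activity among the characteristics on which the substudy is selected.
4. Separately, check the two outdoor-frequency cells against the data. Values of about 1.4% (diary-only, less than once a week) and 12.6% (not in substudy, 4–6 times a week) would restore the totals.

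The cost is one re-run test, one rewritten sentence and two cells to verify. No new data are needed.

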## Discussion

The purpose of this paper was to present the study protocol of LISPE project. The aim of the LISPE project is to examine how home and neighborhood characteristics influence the residents’ health, functioning, disability, quality of life and life-space mobility in the context of aging.

### Strengths

We were able to recruit a large group of older people in the LISPE project. This means that the study has sufficient power to detect also moderate relations. To obtain a large study population we chose to collect data in personal face-to-face interviews in the participants’ homes. This has the advantage of enabling persons with poorer health to take part. We also know for certain that the intended member of the household was interviewed. In addition, in cases where the participant did not immediately understand the question, the interviewer was able to assist by repeating the question or by providing examples. The home visit also allowed for an objective assessment of the home environment and a performance test in a setting familiar to the participant.

In addition to the face-to-face interview, a large proportion of our participants were willing to participate in our substudy on walking activity and life-space mobility. Compared to previous studies using accelerometer data, our sample size is large. Although the substudy the study participants were somewhat more physically active, the sample also includes older people who reported very little physical activity. In addition, the possibility to combine the accelerometer and diary data with the data collected in the baseline and follow-up interviews, provides a unique research opportunity.

We provided the interviewers with a comprehensive training for their task. The quality assurance system and CAPI method worked well and resulted in quick completion of the analytical datasets. Consequently, the quality of the data is good with very few missing data.

### Limitations

Our goal was to recruit older people with wide variability in mobility. Unfortunately, the non-respondent analysis revealed that those with more mobility problems were more likely to decline participation. Consequently, those with worse mobility are underrepresented in the study. However, this is a common challenge in research among older people
[66]. Moreover, we wanted to include participants in different living environments; in the event, we managed to recruit only a limited number of participants in rural areas. Therefore, for this segment of the sample the analyses will be somewhat limited as far as rural dwellers are concerned, although, according to our power analyses, it should still be possible to perform univariate correlations.

We have collected data over a period of six months, starting in winter and ending in summer. The climate in central Finland is characterized by cold winters with ice and snow, and moderately warm summers. Consequently, the extended data collection period may have introduced additional variability in life-space mobility. Although the outdoor temperatures may not affect the lives of the Finnish people too much, people are more likely to stay indoors in winter to avoid walking on slippery surfaces. In this study, it is possible to take outdoor temperature into account. It should also be borne in mind that a wide range of weather conditions are a fact of life in our study area. Consequently, the six-month data collection period may increase the face-validity of the data.

Our participants were rather old at baseline and therefore we tried to restrict the length of the interview so as not to burden them too much. Consequently, some aspects relevant for life-space mobility have possibly been left out of the study. For example, we were able objectively to assess physical fitness only for lower extremity performance.

## Conclusions

A specific strength of this study is that we have collected data on a topic important for aging societies. We have used a novel approach which enables us to study the interactions between environmental features and individual characteristics that underlie the life-space of older people. The results of this study have the potential to contribute to improvements in strategies to postpone or prevent progression to disability and loss of independence.

## Abbreviations

ADL: Activities of Daily Living; CAPI: Computer-Assisted Personal Interviewing; CES-D: Centre for Epidemiologic Studies Depression Scale; HE: Housing Enabler; IADL: Instrumental Activities of Daily Living; IPA: Impact on Participation and Autonomy; LISPE: Life-Space Mobility in Old Age; LSA: Life-Space Assessment; MMSE: Mini-Mental State Examination; SCAMOB: Screening and Counseling for Physical Activity and Mobility; SPPB: Short Physical Performance Battery; WHOQOL-BREF: World Health Organization Quality of Life Scale Short Version.
